### Considerations for sample size

In the maximum tolerated dose (MTD) level we will treat 3 additional patients (*n* = 6 in total). This number is based on a power calculation (α = 0.05, power = 0.8) to enable detection of a 33% decrease, as compared to untreated tumours, in the expression of Treg frequencies in the primary tumour based on recent data (unpublished) showing 38.1% Tregs (SD of 10.5) of all CD4+ T cells present in primary cervical tumours (*n* = 5). If no DLTs or treatment related SAEs are observed in the 3 different dose cohorts (5, 10, 20 mg) and no clear (systemic) immunological responses are detected based on T cell levels and FACS immunomonitoring, we will add an extra dose cohort of 3 patients treated with 50 mg durvalumab i.t. based on the same criteria as stated in this protocol. Therefore the sample size is at minimum 3 patients and at maximum 24 patients.

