#### Analysis of secondary endpoints (immune parameters)

Frequencies and activation status of the aforementioned immune cell subsets will be analyzed before and after treatment. We will use standard paired or unpaired parametric T or non-parametric Mann Whitney U tests for comparisons between groups and one-way repeated measures ANOVA for follow-up analyses over time

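### The 80% power stated for six patients at the MTD level holds only if the untreated Treg mean, estimated from five tumours, is taken as known without error

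*Protocol article*

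**What the plan says.** Under Considerations for sample size, the protocol article expands the MTD level by three patients to six and gives a statistical reason: "This number is based on a power calculation (α = 0.05, power = 0.8) to enable detection of a 33% decrease". The target is "detection of a 33% decrease, as compared to untreated tumours, in the expression of Treg frequencies in the primary tumour". The inputs are unpublished data "showing 38.1% Tregs (SD of 10.5) of all CD4+ T cells present in primary cervical tumours", from five tumours.

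The paragraph does not say whether the test is one- or two-sided, which test was assumed, or how many untreated tumours the treated ones will be compared with. The five tumours are given as the source of the mean and SD; they are not expressly named as the comparison group.

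Under Analysis of secondary endpoints (immune parameters), the article says: "We will use standard paired or unpaired parametric T or non-parametric Mann Whitney U tests for comparisons between groups". No test is assigned to the tumour Treg comparison. The same section also foresees analysis of immune subsets before and after treatment.

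**The concern.** The mean of a comparison group estimated from five tumours carries sampling error. With an SD of 10.5 its standard error is 10.5/√5 = 4.7 points, over a third of the 12.6-point effect to be detected. A calculation that omits this error overstates power for any comparison with those tumours.

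This power statement is the only justification the article gives for the number of patients at the MTD level. The article's Conclusion expects the immunoassays to help select the dose and target population for later studies. If the Treg comparison shows no difference, a reader who trusts the 80% could take it as good evidence against a one-third reduction when it is not.

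**Working it through.** **Inputs (Considerations for sample size).** Untreated mean 38.1%; SD 10.5; relative decrease 33%; α = 0.05; target power 0.80; six treated patients; five tumours behind the mean and SD. Assumption: the same SD in treated tumours.

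**Effect size.** 0.33 × 38.1 = 12.57 points; d = 12.57/10.5 = 1.197. Reading 33% as one third gives 12.70 points and d = 1.210, which changes little.

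**Step 1: reproduce n = 6.** Take 38.1% as a fixed constant.
- Two-sided normal formula: n = (1.96 + 0.842)²/1.197² = 5.47, rounded up to 6.
- One-sided one-sample t, n = 6: noncentrality 1.197 × √6 = 2.93, 5 df, critical value 2.015; power 80.7%. At n = 5 it is 71.0%, so 6 is the smallest number that works.
- Two-sided one-sample t, n = 6: power 65.3%; n = 8 would be needed (82.6%).

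So 6 follows from the stated inputs by two routes, both with a fixed reference value.

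**Step 2: let the untreated mean carry its error.** Unpaired t, 6 treated against 5 untreated: noncentrality 1.197/√(1/6 + 1/5) = 1.98, 9 df.

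| Test, 6 vs 5 | Power |
|---|---|
| t, two-sided (critical value 2.262) | 42.4% |
| t, one-sided (critical value 1.833) | 57.2% |
| Mann-Whitney, two-sided exact (simulated) | about 31% |

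Sensitivity: if the treated SD fell in proportion to the mean (to about 7.0), simulated two-sided power would be about 56% by pooled t and 49% by Welch.

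**Step 3: what would give 80%.**
- At 6 vs 5, two-sided: d = 1.907, that is 1.907 × 10.5 = 20.0 points, or 20.0/38.1 = 53% relative.
- With six treated patients and a 33% decrease: about 84 untreated tumours two-sided (80.0%), or about 20 one-sided (80.3%).
- With equal groups, two-sided: 12 per group.
- With only five untreated tumours, two-sided power cannot pass Φ(1.197 × √5 − 1.96) = Φ(0.72) = 76%, however many patients are treated.

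**Step 4: cost of the fixed-reference route.** If the mean of five tumours is tested against as though it were a constant, simulation with equal SDs puts the true type I error of the one-sample t-test at about 12% one-sided and 14% two-sided, against the nominal 5%.

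**Step 5: the before/after reading.** With six pairs and SD 10.5 on each occasion, the SD of the change is 10.5 × √(2(1 − r)). Two-sided power is 39% at r = 0, 52% at 0.3, 65% at 0.5 and 85% at 0.7. The article gives neither r nor an SD of change, so these are illustrations over an assumed range.

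**The case against.** The strongest counter-case is that the plan's figure is reproducible. A one-sided one-sample t-test uses the small-sample distribution and gives 80.7% at n = 6, so this is not an arithmetic slip. That stands. A reader might infer from the 6-versus-5 result that the plan flatly fails to deliver 80%, or that its power simply is 42%. The document does not support either statement: sidedness is not given, and the five tumours are named only as the source of the mean and SD. More untreated tumours could be used in the eventual comparison.

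What does not stand is that the fixed-reference route describes the planned comparison. The target is worded against untreated tumours, and the listed between-group tests are t and Mann-Whitney; none is a test against a fixed value.

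The paired option is also listed, and pre- and post-treatment tissue is planned. It could reach 80%, but only with a within-patient correlation that the article does not state, and a comparison with untreated tumours reads more naturally as unpaired.

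Finally, Treg frequency is a secondary outcome, the Conclusion calls the immune work exploratory, and no MTD or escalation rule uses this test. That is correct and limits the severity.

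**Conclusion.** The concern holds in a conditional form. Six patients give 80% power for a 33% decrease only if 38.1% is treated as known without error, with either a one-sided t-test or a two-sided normal approximation. That does not match a comparison with sampled untreated tumours.

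If the five tumours, the only untreated ones with a stated number, form the comparison group, power is about 42% two-sided or 57% one-sided by t-test, and about 31% by two-sided Mann-Whitney. These figures assume a common SD of 10.5, itself estimated from five tumours.

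Severity is moderate: the primary safety objective and the MTD determination are unaffected. The risk is that a null Treg result is read as an 80%-powered negative.

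**What to change.** In Considerations for sample size, restate the power for the comparison actually planned and name the test, the sidedness and the number of untreated tumours. If that is 6 vs 5, say that two-sided power for a 33% decrease is about 42% and that 80% applies to a decrease of about 53%. If 38.1% is meant as a fixed reference, say so, and state that its sampling error is ignored.

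Present the MTD-level Treg comparison as estimation: the difference with a 95% confidence interval. At 6 vs 5 and SD 10.5 the expected half-width is about 2.262 × 10.5 × √(1/6 + 1/5) = 14.4 points, wider than the 12.6-point target, which shows plainly what the data can say.

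The before/after comparison already planned can be reported alongside, with its assumed within-patient correlation stated. Making it the key analysis, pooled over doses, is a trade-off rather than a correction: it would assume a common effect across doses, complete archival pairs and an assay equivalent to the one behind the 38.1%.

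Cost: a reworded paragraph and a less favourable stated figure. No extra patients or samples.

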### Statistical analysis

Tabular summaries will be presented by cohort. Categorical data will be summarized by the number and percentage of subjects in each category. Continuous variables will be summarized by descriptive statistics.

#### MTD evaluation

The MTD will be based on the occurrence of any DLTs. Any DLTs will be summarized or listed.

#### Analysis of safety endpoint(s)

Safety analyses will include AEs, SAEs, changes in laboratory findings, vital signs, performance status and physical examinations. The number of patients reporting (S)AEs will be summarized. The treatment related (S)AEs will be summarized as well. Adverse events will be graded according to the NCI CTCAE v4.03. Similarly, laboratory abnormalities will be graded according to the NCI CTCAE v4.03, if applicable.

#### Analysis of secondary endpoints (immune parameters)

Frequencies and activation status of the aforementioned immune cell subsets will be analyzed before and after treatment. We will use standard paired or unpaired parametric T or non-parametric Mann Whitney U tests for comparisons between groups and one-way repeated measures ANOVA for follow-up analyses over time

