## Methods/design

### Study design

‘DURVIT’ is a non-randomized, single-arm, open-label, phase I study. Patients with cervical cancer who are scheduled for (radical) hysterectomy with lymph node dissection will be enrolled at the Amsterdam UMC (formerly: Academic Medical Center (AMC), Amsterdam). Two weeks before the patient is scheduled for surgical treatment, durvalumab (AstraZenecaBV) will be injected locally into the cervix (Fig. 1). Three doses of durvalumab will be tested in a 3 + 3 dose escalation design: 5, 10 and 20 mg intratumourally (i.t.) (Fig. 2). If no dose limiting toxicities (DLTs) or treatment related serious adverse events (SAEs) are observed in the 3 different dose cohorts (5, 10, 20 mg) and no clear (systemic) immunological responses are detected based on T cell levels and FACS immunomonitoring, we will add an extra dose cohort of 3 patients treated with 50 mg durvalumab i.t. based on the same criteria. The Common Terminology Criteria for Adverse Events (CTCAE) v4.03 will be used for the assessment of adverse events.

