**Fig. 2 Fig2:**
[figure not shown]
DURVIT study flowchart. DLT = dose limiting toxicity, SAE = serious adverse event, MTD = maximum tolerated dose

Pre-treatment archival formalin-fixed, paraffin-embedded (FFPE) tissue samples will be requested from centres where patients were diagnosed or had their primary treatment. Post-surgery tumour and lymph node material will be fixed and stored. To have a complete clinical characterization of the patients included in this study, we will perform the standard diagnostic HPV typing for our institution: the HPV Risk Assay (Self-Screen) [33]. Blood samples will be taken once during the screening period, at day 0 (prior to durvalumab administration, i.e. at baseline), at day 14 (at the time of surgery), after 4 weeks, and at 3 months after administration of durvalumab. Post-surgery biopsies of the removed tumour and sentinel and non-sentinel TDLN samples will be collected and processed as described previously [27].

The trial has been approved by the Institutional Review Board of the Academic Medical Center (AMC) and sponsored by the AMC, with funding from Stichting Vrije Universiteit Medical Center - Cancer Center Amsterdam (VUmc-CCA) and Astra Zeneca for the immunological tests (requested). Electronic data is submitted by the study staff via the online database CastorEDC. The study will be monitored by the Clinical Research Unit of the AMC. The first patient has been included in this trial in November 2017.

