## Conclusion

For the first time in cervical cancer, intratumoural administration of an immune checkpoint inhibitor will be investigated primarily for safety. We believe we will also be able as an exploratory objective, to unravel in a quantitative and qualitative manner the effect of the PD-L1 inhibitor durvalumab on the microenvironment in the primary tumour, the tumour draining lymph nodes and, importantly, on the systemic immune response. The proposed correlative immunoassays will shed light on mechanisms underlying the biological effects of PD-L1 blockade and may demonstrate its biological efficacy. These tests will aid in the selection of optimal dose and target population for subsequent studies, and facilitate a rational approach to the design of later phase 2 trials of this novel immunotherapy strategy.

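### The between-group tests named for immune parameters are not tied to each patient's pre-treatment value, although that value is collected for blood and, where archival tissue is obtained, for tumour immunohistochemistry

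*Protocol article*

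**What the plan says.** The section on secondary endpoints opens with a before/after aim: "Frequencies and activation status of the aforementioned immune cell subsets will be analyzed before and after treatment". It then names the methods. For groups: "We will use standard paired or unpaired parametric T or non-parametric Mann Whitney U tests for comparisons between groups". For time: "one-way repeated measures ANOVA for follow-up analyses over time". The groups are not defined, and the response variable (follow-up value or change) is not stated.

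Study design schedules blood at screening and then "at day 0 (prior to durvalumab administration, i.e. at baseline), at day 14 (at the time of surgery), after 4 weeks, and at 3 months". Archival pre-treatment tissue is to be requested from the diagnosing centres, and Outcome measurements plans IHC on pre- and post-treatment material. Fresh tissue for flow cytometry (FACS) comes only at surgery: "Post-surgery biopsies of the removed tumour and sentinel and non-sentinel TDLN samples will be collected".

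The Conclusion says of the immune assays: "These tests will aid in the selection of optimal dose and target population for subsequent studies". The trial is a "non-randomized, single-arm, open-label, phase I study" with cohorts at 5, 10 and 20 mg, three patients each and three more at the highest tolerated dose.

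**The concern.** If the assays are to inform dose, someone will compare immune values across dose cohorts. No named method carries both a dose term and the patient's baseline:

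- A paired t test compares before with after within patients, not different patients on different doses.
- A one-way repeated measures ANOVA has time as its only factor.
- That leaves the unpaired t or Mann-Whitney test. Run on day-14 values alone, it keeps stable differences between patients in the error term.

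With three to six patients per dose, that spread can hide a real dose difference, although the measurement that would remove much of it is already being taken.

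**Working it through.** **The plan's own figure.** The only power calculation, in Considerations for sample size, concerns tumour Tregs against untreated tumours. A 33% fall from 38.1% is 12.57 points. With SD 10.5, the one-sample normal formula gives ((1.960 + 0.842) × 10.5 / 12.57)² = 5.5, so n = 6, as stated. It says nothing about dose comparisons or baseline adjustment. No figure in the article addresses this point.

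**Inputs.** From the article: cohorts of 3, 3 and 6 at 5, 10 and 20 mg (taking 20 mg as the level with three additional patients). Assumed: a true difference of 1.5 SD between lowest and highest dose, linear in log dose; equal SD at baseline and follow-up; normal data; two-sided 5% level; r from 0.3 to 0.85.

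**Pooled analysis, N = 12.** Code log dose as d = 0, 0.5, 1. Its mean is (3×0.5 + 6×1)/12 = 0.625. Its sum of squares is 3(0.625)² + 3(0.125)² + 6(0.375)² = 2.0625.

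- *Follow-up only:* noncentrality 1.5 × √2.0625 = 2.15 on 10 df (critical t 2.228). Power 49%.
- *Change from day 0:* error variance is 2(1 − r) times the follow-up variance, so the noncentrality is 2.15/√(2(1 − r)).
- *Baseline as covariate:* error variance is (1 − r²) times the follow-up variance, multiplied by 1 + 1/(N − 4) = 1.125 for estimating the slope, on 9 df (critical t 2.262). Power and interval width were simulated (200,000 trials per scenario).

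| r | Variance ratio, covariate | Variance ratio, change | Power, follow-up only | Power, change | Power, covariate | Mean 95% interval width, covariate (follow-up only: 3.03 SD) |
|---|---|---|---|---|---|---|
| 0.3 | 0.91 × 1.125 = 1.02 | 1.40 | 49% | 38% | 48% | 3.09 SD |
| 0.5 | 0.75 × 1.125 = 0.84 | 1.00 | 49% | 49% | 56% | 2.80 SD |
| 0.7 | 0.51 × 1.125 = 0.57 | 0.60 | 49% | 71% | 72% | 2.31 SD |
| 0.85 | 0.28 × 1.125 = 0.31 | 0.30 | 49% | 94% | 93% | 1.70 SD |

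Type I error at zero effect was about 5% for all three.

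**Isolated pairs of cohorts, same 1.5 SD effect.**

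- *3 v 3:* the slope penalty is 1 + 1/2 = 1.5 and critical t rises from 2.776 to 3.182. Power is 29% unadjusted. With the covariate it is 23%, 26%, 36% and about 55% at r = 0.3, 0.5, 0.7 and 0.85. Change from day 0 gives 29%, 44% and 71% at r = 0.5, 0.7 and 0.85.
- *3 v 6:* 45% unadjusted. With the covariate it is 41%, 48%, 64% and about 87%.

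The covariate model is therefore worth using on the pooled cohorts, not on a 3 v 3 pair.

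**The case against.** A reader might infer four stronger things, which the article does not support.

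- *That the named tests cannot use a baseline.* They can: an unpaired t or Mann-Whitney test may be run on change from day 0, and nothing restricts them to follow-up values. At r of 0.7 or more this recovers essentially all of the gain. It is the worse choice at low r, and r is unknown.
- *That about half the precision is thrown away.* In large samples that needs 1 − r² = 0.5, so r of about 0.71. No correlation is given. At r = 0.3 adjustment gains nothing in this trial.
- *That a planned dose test is invalid.* No dose hypothesis is written. The stated aim is before versus after, cohorts are summarised descriptively, and the immune work is called exploratory. The unadjusted figure above is also a log-dose regression, not a test that the article names, so the contrast shows what the baseline is worth and does not measure the article's own analysis.
- *That the remedy reaches the powered endpoint.* It does not: tumour Treg frequency by FACS has no pre-treatment value.

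It can also be said that an article commonly leaves the choice of response variable to the full protocol or SAP. That is fair, and it makes the point conditional. What remains is that the article does fix a list of tests for group comparisons, none of them a model with baseline and dose together, while presenting the assays as a guide to dose.

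**Conclusion.** The point holds as a modest, conditional one. If doses are compared on follow-up values alone, the pooled 3+3+6 comparison forgoes nothing at r = 0.3, about 7 points of power at 0.5, 23 at 0.7 and 43 to 44 at 0.85, under the assumed 1.5 SD log-linear effect. The covariate model is the safer choice while r is unknown: it beats change scores at r of 0.5 or below and is within about two points of them above. The gain is in the precision of an exploratory analysis; neither the safety objective nor the validity of the plan is in question. Cohorts are filled in sequence and not randomised, so an adjusted dose difference remains descriptive.

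**What to change.** In the section on secondary endpoints, state that any between-dose comparison of blood parameters, and of IHC parameters with a pre-treatment archival value, will use one exploratory linear model across all treated patients. The outcome is the post-treatment value, the pre-treatment value is the covariate, and dose (for example log dose) is the predictor. Report the estimate with its 95% interval. Say that the model will not be fitted to isolated 3 v 3 pairs, and keep unadjusted tests for tumour and lymph-node FACS parameters, which have no pre-treatment sample.

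Cost: one sentence, one residual degree of freedom, and about 1 to 2 points of power if r is about 0.3. No new data are needed.

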**Methods:**

DURVIT is a non-randomized, single-arm, open-label, phase I study. Three escalating dose levels of intratumourally (i.t.) injected durvalumab will be tested, i.e. 5, 10 and 20 mg (three patients per dose level, with an additional three at the highest tolerated dose). The primary endpoint of this phase-I study is safety. Immune monitoring will consist of flow cytometric, immunohistochemical and functional T cell reactivity testing. The first patient has been included in this trial in November 2017.

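### The repeated-measures ANOVA for serial blood immune parameters uses only complete series and can be mildly anti-conservative; a simple mixed model on all samples is a cheap improvement

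*Protocol article*

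**What the plan says.** Under the analysis of secondary endpoints, the protocol article lists paired or unpaired t tests or Mann-Whitney U tests for comparisons, and "one-way repeated measures ANOVA for follow-up analyses over time". It names no sphericity correction and no rule for incomplete series.

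The blood schedule is in the study design section: "Blood samples will be taken once during the screening period, at day 0" (before the injection), then "at day 14 (at the time of surgery), after 4 weeks, and at 3 months after administration of durvalumab". Tissue is described only as pre- and post-treatment material, so the over-time analysis can in practice concern only blood.

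On numbers, the abstract plans "three patients per dose level, with an additional three at the highest tolerated dose", which is 3 × 3 + 3 = 12 if all three doses are tolerated. The sample size section gives a range: "Therefore the sample size is at minimum 3 patients and at maximum 24 patients". The primary endpoint is safety. The immune parameters are secondary outcomes, and the conclusion calls them exploratory.

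**The concern.** Classical one-way repeated-measures ANOVA needs a value at every visit for every patient. A patient with one missing sample leaves the analysis with all her other samples. Its F test is exact only under sphericity, meaning that the differences between any two visits all have the same variance. Surgery falls at day 14, and the background section says that some patients receive adjuvant (chemo)radiation. The later samples could therefore vary more than the early ones, and samples far apart in time could be less alike than neighbouring ones.

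What is at stake is the precision, and to a lesser degree the error rate, of the systemic immune findings. The conclusion says these will help to choose dose and target population for later studies. With about a dozen patients, each one dropped is a noticeable share of the information.

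**Working it through.** **The plan's own figure.** The only power calculation gives 6 patients at the maximum tolerated dose, from "showing 38.1% Tregs (SD of 10.5) of all CD4+ T cells present in primary cervical tumours" and a 33% decrease. The difference is 0.33 × 38.1 = 12.57 and 12.57 / 10.5 = 1.197 SD. The two-sided one-sample normal formula gives (1.96 + 0.84)² / 1.197² ≈ 5.5, rounded up to 6, so the figure reproduces. It concerns tumour Treg frequency and says nothing about the blood series. For blood the article gives no SD, correlation or missing rate, so what follows rests on assumptions.

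**Complete series.** If each sample is missing independently with probability m, the expected number of complete series among n patients is n × (1 − m)^k for k visits. For n = 12:

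| Assumed m | k = 4 (without screening) | k = 5 (with screening) |
|---|---|---|
| 2% | 12 × 0.922 = 11.1 | 12 × 0.904 = 10.8 |
| 5% | 12 × 0.815 = 9.8 | 12 × 0.774 = 9.3 |
| 10% | 12 × 0.656 = 7.9 | 12 × 0.590 = 7.1 |

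This pools all dose levels. For the 6 patients at one dose, k = 4 gives 4.9 at 5% and 3.9 at 10%.

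**Power of the over-time test.** In a simulation with n = 12, four visits and an assumed equal correlation of 0.6, a patient-plus-visit model on all samples was compared with the complete-case ANOVA. With nothing missing the two tests are identical. At 5% missing per visit, power was 69% against 61%; at 10% it was 65% against 51%. The losses are 69 − 61 = 8 and 65 − 51 = 14 percentage points. The absolute levels depend on the assumed time profile, which the article does not give. Other assumed profiles showed a loss in the same direction.

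**Type I error of the uncorrected F test.** Nominal 5%, n = 12, visits at days 0, 14, 28 and 90, simulated under no change over time:
- Equal correlation and equal SDs: 5.1%, so no inflation.
- Correlation decaying at 0.5, 0.7 or 0.9 per 14 days, equal SDs: 5.9%, 6.9% and 7.7%. With a screening sample assumed at day −14: 5.7%, 7.0% and 8.3%.
- Equal correlation, SDs 1, 1, 1.5, 2: about 6% to 7%. SDs 1, 1, 2, 3: about 8% to 9%, depending on the correlation.
- Correlation decaying at 0.8 per 14 days and SDs 1, 1, 1.5, 2 together: about 8% to 9%. Adding a fifth visit gives 9.5%, the highest value found.
- The same decaying-correlation settings with the Greenhouse-Geisser correction: 3.4% to 4.8%.

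**The case against.** The strongest reply is that this is a standard caveat on an exploratory analysis, and much of that reply stands.

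- A reader might infer that a missed 3-month visit discards the day-0 to day-14 change. That is so only inside the ANOVA. The same section says the immune subsets will be analysed before and after treatment and names paired tests, which use every patient with both samples.
- A reader might infer that uneven visit spacing by itself invalidates the test. It does not, because visit enters as a factor. The requirement is sphericity, which is weaker than equal correlation and unrelated to spacing as such.
- A reader might infer that the error rate is certainly inflated. It depends on an unknown covariance, and the usual correction within the same ANOVA removes it. The article neither names nor excludes that correction, which may stand in a fuller document, so its absence is not itself a fault.
- A reader might infer that patients will be lost. The article gives no missing rate. The day-14 sample is taken at surgery and the 3-month sample coincides with the end of the toxicity evaluation period, so losses may be small. At 2% per visit about 11 of 12 series are complete.
- A rich mixed model would be no improvement. An unstructured covariance over five visits has 5 × 6 / 2 = 15 parameters, too many for about 12 patients. Visit-specific variances on top of a random intercept are also fragile at this size.

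What remains is that the article does commit to a method that uses only complete series. The sphericity correction does not bring incomplete patients back.

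**Conclusion.** The point holds as a modest improvement, not as an error that threatens the trial. The named ANOVA gives away samples whenever a series is incomplete. At an assumed 5% to 10% missing per visit over four visits, that is about 2 to 4 of 12 patients (12 − 9.8 = 2.2; 12 − 7.9 = 4.1) and roughly 8 to 14 points of power for the over-time test. Without a correction it can also be mildly anti-conservative, about 6% to 9% instead of 5% at n = 12, and not at all under sphericity. The missing rates, correlations, SDs and time profile are all assumptions. Twelve is the planned path within a stated range of 3 to 24.

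The safety conclusion is unaffected. The article makes the absence of a clear immunological response one condition for an extra dose cohort, but it does not tie that judgement to this test, so no effect on that decision can be claimed.

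**What to change.** In the analysis of secondary endpoints, replace the one-way repeated-measures ANOVA by a linear mixed model fitted to all available samples. Use visit as a categorical factor, a patient random intercept and Kenward-Roger degrees of freedom. Report the day-14 minus day-0 contrast with its 95% interval from all available pairs.

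Add a complete-case ANOVA with the Greenhouse-Geisser correction as a sensitivity check on the over-time test. This is needed because a random intercept also assumes equal correlation and equal variance. The mixed model recovers the incomplete patients, and the corrected ANOVA guards the error rate. The model also assumes that missingness depends only on observed data, which should be stated.

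The cost is a sentence or two of wording and slightly more programming. With complete, spherical data the answer is the same as from the ANOVA.
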